#### Secondary outcomes

The NRS pain score will also be measured at the end of the last treatment each week (weeks 1, 2, 3, 4, and 5). Other secondary outcomes will include the changes in WOMAC, SF-36, knee circumference, and 6-min walking test (6MWT) from baseline to endpoints (weeks 6 and 10):WOMAC: This scale evaluates the comprehensive condition of the knee joint from three aspects: knee pain, stiffness, and daily functional activities. The WOMAC scale contains 24 items, with four points for each item. A higher score signifies worse knee function. The Chinese version of this scale has good reliability and validity [39].SF-36: This scale consists of 36 items, including eight fields of physical function, arole physical, physical pain, general health status, vitality, social function, arole emotional, and mental health, and is used to assess the health-related quality of life of the subject. A higher score indicates better health-related quality of life [40, 41].Knee circumference: The degree of swelling in the subject’s knee was assessed by measuring the knee circumference (i.e., the leg circumference at the center of the upper and lower edges of the patella) in millimeters. A uniform tape measure will be used to measure different patients [42].6MWT: Before the test, researchers will draw a 30-m straight line on flat ground and mark both ends of the line. During the test, the participants will walk back and forth in a straight line at their own speed. The researchers will give the correct time every two minutes and calculate the distance walked by the participant at the end of six minutes. Potential discomfort such as fatigue, dizziness, angina pectoris, dyspnea and cold sweat will be recorded during the trial. The trial will be suspended or discontinued if the patient cannot complete it. During the test, participants will be monitored with a unified wristwatch for basic indicators such as heart rate and blood oxygen. The Borg score of dyspnea and fatigue and other data will be recorded before and after the test (Table 2) [43].

**Table 2 Tab2:**
[figure not shown]
Schedule of enrolment, interventions and assessments

*CRP test,* C-reactive protein test; *WOMAC*, Western Ontario and McMaster Universities Osteoarthritis Index; *SF-36*, 36-item Short-Form; *6MWT*, 6-min walking test

### Safety assessment

The safety assessment will primarily include the recording of adverse events (AEs) and serious AEs, laboratory analyses, and monitoring throughout the exercise test. AEs occurring during treatment and follow-up will be recorded by the investigator on AE questionnaires within 24 h of their occurrence. In addition to recording the time, severity, reaction, treatment, and prognosis of the AEs, the questionnaire will also focus on recording the potential relationship between AEs and TM or ILM treatment. The most common treatment-related AEs include skin redness, pruritus, scalding, blisters, and dizziness. If the AE is severe, the patient will be suspended or withdrawn from the study and receive corresponding medical care or compensation. In addition, blood routine and C-reactive protein (CRP) measurement will be conducted before and after treatment. Lastly, a uniform sports wristwatch will be used to monitor the participants’ heart rates during the 6-min walk test.

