**Materials and methods:**

In the designed Zelen-design randomized controlled non-inferiority clinical trial, a total of 74 patients with KOA will be randomly allocated to one of two interventions: ILM treatment or TM treatment. All participants will receive a 6-week treatment and a follow-up 4 weeks after treatment. The primary outcomes will be the mean change in pain scores on the numeric rating scale (NRS) measured at baseline and the end of last treatment at week 6. The secondary outcomes will be the pain scores on the NRS from weeks 1 to 5 after the start of treatment and the changes from baseline to endpoints (weeks 6 and 10) in the Western Ontario and McMaster Universities Osteoarthritis Index (WOMAC), SF-36, knee circumference, and 6-min walking test. In addition, safety assessment will be performed throughout the trial.

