### Sample size calculation

This study is a randomized controlled non-inferior trial. Based on the literature, the smallest clinically significant difference in the pain NRS is 2 points [44–46]. Thus, we set the non-inferiority margin to − 2. The NRS score of the subjects after treatment was taken as the main outcome index. According to the results of similar studies, [47] the average NRS score of the experimental group was 40.53 ± 26.63, and that of the control group was 41.58 ± 15.07. So we used PASS 15 to calculate the sample size (29 participants in each group), *α* = 0.025, 1 − *β* = 80%. Considering that a maximum of 25% dropped out during the trial, we ultimately plan to recruit 74 participants (37 in each group) to ensure the target sample size is obtained. The calculation results of sample size are provided as Additional file 2.

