### Statistical analysis

Statistical analysis will be undertaken using both intention-to-treat (ITT) and per-protocol (PP) analyses. For the ITT analysis, all patients who undergo the Zelen-type randomization and received at least one treatment will be analyzed. Primary PP data analysis will also be undertaken for all patients who have high compliance (patient compliance rates equal to or greater than 80%) and do not use drugs or treatments prohibited by the protocol during treatment.

The statistical analysis will take the form of a non-inferiority test. The margin of non-inferiority is -2. For the main outcome, we will calculate the 95% confidence interval for the difference in NRS pain score between the treatment group and the control group. If the lower limit is greater than -2, non-inferiority will be considered valid.

For continuous data, mean ± standard deviation will be used to describe data that conforms to a normal distribution, whereas non-normally distributed continuous data will be described as the median (interquartile spacing). Where the data conforms to a normal distribution, independent sample t-test will be used for comparison between the two groups with homogeneity of variance; otherwise, a t-test will be used with heterogeneity of variance. Wilcoxon rank-sum test will be used if data does not conform to a normal distribution. Categorical data will be represented by frequency or percentage and compared using chi-square test or Fisher exact test. Missing data will be replaced according to the last observation carried forward method. The 95% confidence interval will be calculated, and *P* < 0.05 will be considered to indicate a significant difference. All statistical analysis will be performed using SPSS software (version 20.0).

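### The severe-AE rule does not separate stopping moxibustion from leaving assessment, so a withdrawn participant's week-6 NRS is carried forward when it could have been observed (cheap improvement, probably small effect)

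*Protocol article*

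**What the plan says.** All references are to the protocol article.

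- **Safety assessment**, severe events: "If the AE is severe, the patient will be suspended or withdrawn from the study and receive corresponding medical care or compensation". The rule names the study, not the treatment. No section shown provides for stopping moxibustion while assessments continue.
- **Safety assessment**, recording: "AEs occurring during treatment and follow-up will be recorded by the investigator". The questionnaire also covers the course of each event: "In addition to recording the time, severity, reaction, treatment, and prognosis of the AEs".
- **Statistical analysis**, ITT set: "all patients who undergo the Zelen-type randomization and received at least one treatment will be analyzed".
- **Statistical analysis**, missing data: "Missing data will be replaced according to the last observation carried forward method". No other missing-data rule is given.
- **NRS timing**: the Abstract dates the secondary NRS scores "from weeks 1 to 5 after the start of treatment". The Primary outcome and Secondary outcomes sections instead tie the NRS to the final treatment session of the week, and the Abstract does the same for the primary week-6 score.
- **Sample size calculation**: 29 per arm, then "we ultimately plan to recruit 74 participants (37 in each group) to ensure the target sample size is obtained". The margin is 2 NRS points.

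**The concern.** Stopping a treatment and leaving a trial are different events. A patient with a burn or blister may have to stop moxibustion, but can still give a pain score at week 6. The severe-AE rule treats the two as one. Where the patient is withdrawn, the primary outcome is lost by rule rather than by the patient's choice, and LOCF supplies a substitute.

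The missingness would come from a treatment-related event, in an unblinded non-inferiority comparison whose second aim is to show whether ILM is a safe alternative. If severe events differ between arms, so does the share of imputed primary outcomes, and non-inferiority then depends partly on carried-forward scores. Assessments after a severe event also bear on the safety question.

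**Working it through.** **1. What happens to one participant.** Suppose a severe event in week 3 leads to withdrawal.
- The participant has had at least one treatment and so stays in the ITT set.
- No NRS is taken after withdrawal if the rule is followed as written.
- LOCF puts the last weekly score (the baseline score, if withdrawal comes before the first weekly assessment) in place of the week-6 score.

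If the rule leads only to a temporary pause and the participant returns, the week-6 score may be observed. The point is therefore limited to those withdrawn before week 6.

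**2. The planned numbers.** The 37 per arm is the denominator used below.
- The 29 per arm is reproduced with margin 2, true difference 0, one-sided alpha 0.025, power 80%, and an SD of 2.663 in both arms (the article's 26.63 taken to a 0–10 scale).
- Normal approximation: n = 2 × 2.663² × (1.960 + 0.842)² / 2² = 27.8, so 28. The noncentral-t version gives 29 (power 0.8025).
- 29 × 1.25 = 36.25, so 37.

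No figure in the plan is challenged here.

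**3. Effect on the primary comparison.** Let k be the net number of LOCF-filled participants in one arm and d the error of each filled score against the score that would have been observed, all in the same direction. With 37 per arm in the ITT set (assuming all are treated):

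shift in the mean difference = k × d / 37

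| k (assumed) | d, points (assumed) | Shift, points | Share of 2-point margin |
|---|---|---|---|
| 1 | 1 | 1/37 = 0.027 | 1.4% |
| 1 | 3 | 3/37 = 0.081 | 4.1% |
| 3 | 3 | 9/37 = 0.243 | 12.2% |

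For scale, the standard error of the difference with SD 2.663 and 37 per arm is 2.663 × √(2/37) = 0.619, so the largest shift is 0.243 / 0.619 = 0.39 standard errors. If a shift happened to favour ILM, 0.10 points would raise the one-sided type I error from 0.025 to about 0.036, and 0.20 points to about 0.050. In the other direction it would make the test conservative.

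**4. Could the score be observed off treatment?** Yes, since the outcomes are dated by week. However, the Primary outcome and Secondary outcomes sections anchor the NRS to a treatment session, and a participant off treatment has none. The timing has to be restated for such participants, so rewording the severe-AE sentence alone is not enough.

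**The case against.** **The article condenses a fuller protocol.** Follow-up after stopping treatment may be set out there, and the quality-control section mentions operating procedures and training in adverse-event management that are not shown. This stands as a caution. The point, however, concerns two rules that the article does state, which together give a worse result than necessary.

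**The wording is loose.** Suspension allows return, and in the walking-test paragraph the article speaks of suspending or discontinuing the trial when it evidently means the test. The first part stands and limits the point to withdrawn participants. The second does not turn withdrawal from the study into withdrawal from treatment.

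**Safety recording is covered.** Events are recorded through follow-up and their prognosis is noted, so the index event is followed. A reader might infer that new events after withdrawal go unrecorded. That can be inferred from the withdrawal wording, but the text does not say it.

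**Loss of sample size.** A reader might infer that each withdrawal uses up one of the 37 − 29 = 8 spare places per arm. It does not. ITT loses no one, because LOCF keeps these participants in. The per-protocol set needs at least 80% compliance. If that means sessions (an assumption), it is 0.80 × 18 = 14.4, so 15 of 18. At three sessions a week, anyone stopped before the end of week 5 fails it whether assessed or not.

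**Bias towards ILM.** A reader might infer that severe events will be commoner on TM and that early, higher TM scores carried forward will favour ILM. The article hopes that ILM is safer, but gives no severe-AE rate for either arm and no pain course after stopping. The direction cannot be fixed from the documents.

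**Few would benefit.** Severe events should be rare, since heat is adjustable in both arms, and enrolment was expected to be completed by November 2023. This stands, and it limits the value of the change.

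**Conclusion.** The point holds as a cheap improvement. As written, the severe-AE rule and LOCF together replace an obtainable week-6 NRS with an earlier score for participants withdrawn before week 6. Under the assumed range the shift is 0.03 to 0.24 points, or 1.4% to 12% of the margin. The upper end needs a net 3 of 37 participants (8%) in one arm, all wrong by 3 points in the same direction, so the real effect is probably small. Only 37 and the 2-point margin come from the article; the numbers withdrawn and the errors are assumptions. The documents do not support a stated direction of bias or a claim that the trial loses sample size.

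**What to change.** 1. **Safety assessment:** reword the rule so that a severe event leads to interruption or discontinuation of study treatment only. Unless consent is withdrawn, the participant keeps the scheduled NRS, the week-6 and week-10 assessments and the post-treatment blood tests. Adverse events are followed to week 10 or resolution. When to pause or stop treatment remains a clinical decision.
2. **Primary outcome and Secondary outcomes:** state that, for participants off treatment, the NRS is taken at the same calendar week counted from the start of treatment, instead of after a treatment session.

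The cost is an amendment approved by the Ethics Committee, as the article requires for any change, and a few already scheduled visits attended off treatment. The sample size is unchanged. Only participants still within their 10 weeks when the amendment is approved would benefit.

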### Study quality control and data management

The trial protocol for this clinical study has been reviewed and confirmed by methodological and statistical experts in relevant fields, and the trial will be carried out in strict accordance with this protocol. Any changes to the protocol will need to be approved by the Ethics Committee.

Before the study begins, all researchers involved in the treatment will be instructed and trained in the standardized operating procedures. The training content will include the implementation steps and methods of the project, the operation methods of traditional moxibustion and the infrared ceramic graphene moxibustion device, and the management of adverse events. To ensure the quality and integrity of the trial, each clinical trial site will have a clinical supervisor specializing in acupuncture and moxibustion who will supervise the entire process.

The original data from this project will be recorded in detail in the individual case report forms (CRFs), informed consent form, clinical medical records, laboratory test sheets, and imaging data, all of which are traceable. The investigator will manually fill out the CRFs for all patients. The investigator will indicate their name and the date, periodically collect the data. Any changes made to the data and reasons for any missing data will also be indicated in the notes.

Three months after the publication of the clinical study, the original data will be shared through the ResMan platform of the Chinese Clinical Trial Registry (http://www.medresman.org.cn).

### Sample size calculation

This study is a randomized controlled non-inferior trial. Based on the literature, the smallest clinically significant difference in the pain NRS is 2 points [44–46]. Thus, we set the non-inferiority margin to − 2. The NRS score of the subjects after treatment was taken as the main outcome index. According to the results of similar studies, [47] the average NRS score of the experimental group was 40.53 ± 26.63, and that of the control group was 41.58 ± 15.07. So we used PASS 15 to calculate the sample size (29 participants in each group), *α* = 0.025, 1 − *β* = 80%. Considering that a maximum of 25% dropped out during the trial, we ultimately plan to recruit 74 participants (37 in each group) to ensure the target sample size is obtained. The calculation results of sample size are provided as Additional file 2.

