### Inclusion criteria

The inclusion criteria were as follows:Diagnosed with KOA according to the American College of Rheumatology criteria [28].Aged 40–70 years old.Average pain score of 4 or more out of 10 on the numeric rating scale (NRS) [29].Average severity score of 48 or less on the Western Ontario and McMaster Universities Osteoarthritis Index (WOMAC) [30].Standard radiographs with Kellgren–Lawrence (KL) grade II or III [31].Written informed consent.With basic reading and comprehension skills.

Participants who fulfill the above seven criteria can be included in the trial.

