#### Primary outcome

The primary outcome, to be assessed at the end of the last treatment at week 6, is the change in pain from baseline using the NRS index [38]. The NRS index typically uses a 0–10 range instead of words to represent the degree of pain experienced by the subject: 0 indicates no pain; 1–3 indicates mild pain (occasional pain that generally does not interfere with walking); 4–6 indicates moderate pain (frequent pain that interferes with walking); 7–9 indicates severe pain (sustained pain that seriously interferes with or prevents walking); and 10 indicates the worst/overwhelming pain. At the time of the evaluation, participants will be asked to mark the number on the scale that best represents their pain level in the last 24 h.

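### The sample-size inputs are printed on a scale the 0–10 NRS and its 2-point margin do not share, and 29 per group at 80% power is recovered only with settings the text does not state

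*Protocol article*

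**What the plan says.** In the protocol article:

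- Primary outcome defines the scale: "The NRS index typically uses a 0–10 range". The Inclusion criteria use the same scale, with a minimum score expressed out of 10.
- Sample size calculation takes the margin from the premise that "the smallest clinically significant difference in the pain NRS is 2 points". Statistical analysis repeats it: "The margin of non-inferiority is -2".
- Sample size calculation then gives the planning values from a similar study: "the average NRS score of the experimental group was 40.53 ± 26.63, and that of the control group was 41.58 ± 15.07".
- The result follows directly: "So we used PASS 15 to calculate the sample size (29 participants in each group", with alpha 0.025 and power 80%. Additional file 2, which is not shown, is cited for the calculation.
- The same section names the endpoint used for sizing: "The NRS score of the subjects after treatment was taken as the main outcome index". Primary outcome instead defines the change in NRS from baseline to the end of week 6.

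**The concern.** A score that cannot exceed 10 cannot average 40. The planning values look like a 0–100 pain scale, yet they are called NRS scores and stand beside a margin of 2 NRS points. In a non-inferiority calculation the sample size depends on the ratio of SD to margin, so the two must share a unit before the power statement means anything.

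Even if the reader supplies a division by 10, the two quoted SDs at the stated 80% power do not give 29. The article therefore does not let a reader see which SD, which assumed difference or which scale lies behind 29, nor whether 29 per arm delivers about 80% or over 90% power.

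**Working it through.** **Inputs.** Margin 2; SDs 26.63 (experimental) and 15.07 (control); means 40.53 and 41.58, so the experimental arm is lower by 1.05; alpha 0.025; power 80%; 1:1 allocation. Alpha is taken as one-sided, which matches the rule in Statistical analysis that compares one limit of a 95% confidence interval with the margin.

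**Formula.** Let d be the true disadvantage of ILM in points (positive means ILM is worse; a lower NRS is better). By normal approximation, n per arm = (1.95996 + 0.84162)² × (s1² + s2²) / (2 − d)², and the first factor is 7.849. The exact versions use the noncentral t distribution.

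**Reproducing 29.** Divide by 10, put SD 2.663 in both arms, and set d = 0:

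- 7.849 × 2 × 2.663² / 2² = 7.849 × 14.183 / 4 = 27.8, so 28 by normal approximation.
- The t-test gives 29, with power 80.2% at 29 per arm.

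This matches the stated n and power. It needs the division by 10, drops the quoted control SD and ignores the quoted difference in means.

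**As printed.** s1² + s2² = 709.16 + 227.10 = 936.26, and 7.849 × 936.26 = 7,349.

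- d = −1.05: 7,349 / 3.05² = 790
- d = 0: 7,349 / 2² = 1,838 (rounded up)
- d = +1.05: 7,349 / 0.95² = 8,143

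Power with 29 per arm is about 8%, 5% and 4% respectively.

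**Divided by 10.** With both quoted SDs, s1² + s2² = 9.3626. With the larger SD in both arms, the sum is 14.183.

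| SDs | d | n per arm at 80%, normal | n per arm at 80%, t | Power at 29 per arm |
|---|---|---|---|---|
| 2.663 and 1.507 | −0.105 | 17 | 18 | 95% |
| 2.663 and 1.507 | 0 | 19 | 20 | 93% |
| 2.663 and 1.507 | +0.105 | 21 | 22 | 90–91% |
| 2.663 in both | −0.105 | 26 | 27 | 84% |
| 2.663 in both | 0 | 28 | 29 | 80.2% |
| 2.663 in both | +0.105 | 31 | 32 | 76% |

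**A second route to 29.** Both quoted SDs, d = +0.105 and 90% power also give 29 by t-test (28 by normal approximation). That is not the stated power, and it reverses the direction of the quoted means.

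**Endpoint.** These SDs are applied to the post-treatment score. The SD of a change from baseline also depends on the baseline SD and on the correlation between the two measurements. The article gives neither, so the power for the change cannot be computed from it.

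**The case against.** The strongest reply is that this is a units slip in one sentence. After division by 10, the larger SD in both arms with no true difference is an ordinary conservative choice, and it returns exactly 29 at the stated alpha and power. The SD per arm and the assumed difference are what software output would normally show, and Additional file 2 may show them. The 790 to 8,143 per arm then describe a calculation that nobody is likely to have run. The margin comes from a clinically significant difference, not from these SDs.

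Most of this stands. A reader might infer that 29 cannot be obtained on either scale, or that 80% is not the power of the design. The documents support neither, because the rescaled larger-SD route gives 29 at 80.2%. A reader might also take the 4–8% as the trial's real power. That would hold only if the printed values were meant literally on the margin's scale, which the 0–10 definition rules out.

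What does not stand is that the supplement cures the text. Nothing in it could make a mean of 40.53 correct as a 0–10 score. The article prints a set of inputs and draws 29 from them, and at 80% power 29 does not follow from those inputs as they stand.

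**Conclusion.** The point holds as an error in the printed inputs and an incompletely stated calculation. The means and SDs are impossible on the trial's NRS and are not in the margin's unit. Assuming that they come from a 0–100 scale and are divided by 10, the two quoted SDs need 18–22 per arm at 80% power, and 29 gives about 90–95%. With SD 2.663 in both arms and no difference, 29 gives 80.2%. The article does not say which of these applies.

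The conclusion rests on the factor of 10, which the article does not state, on one-sided alpha 0.025, and on a two-sample t-test of the post-treatment score. It does not show that the trial is underpowered after rescaling. The only rescaled case above that falls below 80% combines the larger SD in both arms with a true ILM disadvantage of 0.105 (76%), an assumption the article nowhere makes. Nor does it affect the margin. The mismatch between the sizing endpoint and the primary outcome is a further gap, and its size cannot be given from the document.

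**What to change.** In Sample size calculation:

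- Restate the means and SDs on the 0–10 scale, and say that they were converted and how.
- Give the SD entered for each arm and the assumed true difference with its sign.
- State the power that 29 per arm gives under those settings: 80% with SD 2.663 in both arms and no difference, or about 90–95% with the two quoted SDs.
- State that the sizing uses the week-6 score while the primary outcome is change from baseline.
- Check whether Additional file 2 carries the same inputs, and correct it if it does.

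The cost is one re-run of the calculation and a few sentences. The planned 74 participants do not change on account of this point.

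### 37 per group covers about 21% dropout, not the stated 25%: at 25% only 27–28 per group remain of the 29 required

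*Protocol article*

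**What the plan says.** All of the relevant text is in the protocol article, Methods, Sample size calculation, unless another section is named.

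- Evaluable target: "So we used PASS 15 to calculate the sample size (29 participants in each group"), at α = 0.025 and 80% power.
- Allowance for losses: "Considering that a maximum of 25% dropped out during the trial, we ultimately plan to recruit 74 participants (37 in each group").
- Purpose of the allowance: "to ensure the target sample size is obtained".
- Margin: taken from the statement that "the smallest clinically significant difference in the pain NRS is 2 points", and set at −2.
- Planning data: "the average NRS score of the experimental group was 40.53 ± 26.63, and that of the control group was 41.58 ± 15.07".

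The section prints no formula for the step from 29 to 37 and refers to Additional file 2, which is not at hand, for the calculation output. The Statistical analysis section plans two analyses. The intention-to-treat (ITT) set takes everyone randomized who had at least one treatment, and missing values are filled by last observation carried forward (LOCF). The per-protocol (PP) set is limited to participants with at least 80% compliance and no prohibited drug or treatment.

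**The concern.** The section makes four statements: 29 are needed, up to 25% may be lost, 37 are recruited, and 37 secures the 29. They cannot all be true, because three quarters of 37 is less than 29. The number 37 is what results from adding 25% of 29 to 29 and rounding up. That allowance is too small, because the loss applies to the number recruited and not to the number required.

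At stake is the size of any analysis that leaves the dropouts out. In a non-inferiority trial the PP result carries real weight alongside ITT, and the Discussion itself warns that poor adherence can lead to wrongly rejecting the null hypothesis. A reader of the sample size section would believe that the analysis of completers is protected at 25% loss. It is protected only up to a somewhat lower rate.

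**Working it through.** **Inputs.** From Sample size calculation: 29 evaluable per group, maximum dropout 25%, 37 recruited per group, margin 2, α = 0.025 (taken as one-sided, matching the lower limit of a 95% interval), power 80%, means and SDs 40.53 (26.63) and 41.58 (15.07). From Primary outcome: the scale runs from 0 to 10. From Randomization and informed consent: 1:1 allocation.

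**Step 1: reproduce 29.** The printed means and SDs fit a 0–100 scale, whereas the margin and the outcome are on 0–10. Dividing by 10 gives 4.053 (2.663) and 4.158 (1.507). This rescaling is an assumption. With the larger SD in both groups and a true difference of 0, the normal approximation is

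n = 2 × 2.663² × (1.960 + 0.842)² / 2² = 27.8, rounded up to 28,

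and the non-central t calculation gives 29 per group (power 80.2%). That matches the protocol. Using both rescaled SDs separately gives 18–22 per group, which does not match.

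**Step 2: reproduce 37.**

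- 29 × (1 + 0.25) = 36.25, rounded up to 37. This matches.
- 29 / (1 − 0.25) = 38.67, rounded up to 39. This does not match.

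The multiplication is therefore the likely route, but it is inferred from the figures.

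**Step 3: apply the stated dropout to 37.**

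- 37 × 0.75 = 27.75, so 27–28 per group remain, one or two short of 29.
- Largest loss that still leaves 29: (37 − 29)/37 = 8/37 = 21.6%.
- With 39 per group: 39 × 0.75 = 29.25, which meets the target with 78 in total, 4 more than planned.

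This step needs no SD, margin or scale, so it does not depend on the assumptions in Step 1.

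**Step 4: effect on power.** Two-sample t, one-sided α 0.025, margin 2. Distance to the margin = 2 plus the true difference in favour of infrared laser moxibustion (ILM).

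Under the reading that gives 29 (SD 2.663 in both groups, difference 0):

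| Per group | Power |
|---|---|
| 29 | 80.2% |
| 28 | 78.8% |
| 27 | 77.3% |
| 37 (all kept by LOCF) | 89% |

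At 27–28 per group under four readings of the printed inputs:

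| Reading (rescaled to 0–10) | Power |
|---|---|
| SD 2.663 in both, 0.105 against ILM | 72.8–74.4% |
| SD 2.663 in both, difference 0 | 77.3–78.8% |
| SD 2.663 in both, 0.105 in favour of ILM | 81.3–82.8% |
| SDs 2.663 and 1.507, difference 0 | 91–92% |

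The value 0.105 is the difference of the printed means after rescaling: 4.158 − 4.053.

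**The case against.** The strongest reply is that the trial does not lose its power. Dropouts with at least one treatment stay in the ITT set, pain is scored weekly from week 1 to week 5, and LOCF fills the week 6 value, so up to 37 per group can enter that analysis with nominal power of about 89% at SD 2.663. This stands for ITT (whether LOCF is a suitable method is a separate question). It does not dispose of the point. The protocol inflates precisely because it treats dropouts as lost, and early dropouts would fall below the 80% compliance required for PP.

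A second reply is that the power figures rest on settings the article does not state: the rescaling, the larger SD in both groups, and a true difference of 0. This also stands. A reader might infer that the trial fails to deliver its 80% power. The documents do not support that: the figure lies above or below 80% depending on the reading, and even under the reading that gives 29 the loss is only 1–3 points, and only when dropout goes beyond 21.6% towards the stated maximum.

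A third reply is that no inflation formula is printed. That is correct, so the use of 29 × 1.25 should be described as consistent with the figures and not as a fact. The shortfall remains however 37 was reached. The unseen Additional file 2 cannot change it either, since 75% of 37 is below 29 whatever the software settings were.

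**Conclusion.** The headcount claim is wrong as written. At the protocol's own maximum dropout, 37 per group leaves 27–28 and not 29, and the allowance holds only up to 21.6% loss. This follows from the printed numbers alone and is certain.

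The consequence is small and conditional. It applies at the stated maximum dropout, and to an analysis without the dropouts. If 29 was obtained with SD 2.663 in both groups and a true difference of 0, power there is about 77–79% instead of 80%. Across the four readings shown it runs from about 73% to 92%, so the power figure should be quoted only with its assumptions. The margin, the decision rule and the planned analyses are unaffected.

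**What to change.** Keep enrolment at 74 and correct the statement in Sample size calculation. Suggested content: 74 participants (37 per group) retain 29 per group for dropout up to about 21%; at 25% dropout 27–28 per group remain, so power of the per-protocol analysis is slightly below 80% under the assumptions used to obtain 29. State those assumptions next to the figure: the SD used in each group, the scale it is on, and the assumed true difference.

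The cost is one or two sentences and a slightly less favourable stated figure. No design or analysis change follows, and recruitment, already under way according to Trial status, is not affected. If the sponsor prefers to keep the 25% claim, the number that supports it is 39 per group (78 in total), four more participants.
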